# Effectiveness of Checklist-Based Box System Interventions (CBBSI) versus routine care on improving utilization of maternal health services in Northwest Ethiopia: study protocol for a cluster randomized controlled trial

**DOI:** 10.1186/s13063-019-4002-3

**Published:** 2020-02-07

**Keywords:** Box system, Maternal health, Antenatal care, Skilled delivery, Postnatal care, Cluster randomized controlled trial, Ethiopia

## Abstract

**Background:**

Maternal mortality is still high in Ethiopia. Antenatal care, the use of skilled delivery and postnatal care are key maternal health care services that can significantly reduce maternal mortality. However, in low- and middle-income countries, including Ethiopia, utilization of these key services is limited, and preventive, promotive and curative services are not provided as per the recommendations. The aim of this study is to examine the effectiveness of checklist-based box system interventions on improving maternal health service utilization.

**Methods:**

A community-level, cluster-randomized controlled trial will be conducted to compare the effectiveness of checklist-based box system interventions over the routine standard of care as a control arm. The intervention will use a health-extension program provided by health extension workers and midwives using a special type of health education scheduling box placed at health posts and a service utilization monitoring box placed at health centers. For this, 1200 pregnant mothers at below 16 weeks of gestation will be recruited from 30 clusters. Suspected pregnant mothers will be identified through a community survey and linked to the nearby health center. With effective communication between health centers and health posts, dropout-tracing mechanisms are implemented to help mothers resume service utilization. Data will be collected using an open data kit and analyzed using STATA version 13.0. Data will be analyzed by the intention-to-treat analysis. Risk ratios will be computed at the cluster level and the summary will be compared using *t* tests. Outcomes between intervention and control groups will be compared with random effects logistic regression models. Achieving four antenatal care visits, health facility delivery, and postnatal care visits at 6 weeks after delivery were treated as primary outcomes for this study.

**Discussion:**

We expect that the study will generate evidence on the effectiveness of checklist-based box system interventions on improving utilization of maternal health care service that will produce inputs for related policies in Ethiopia.

**Trial registration:**

ClinicalTrials.gov, NCT03891030. Retrospectively registered on 26 March 2019.

## Background

Under-utilization of the key maternal health services of antenatal care (ANC), use of skilled delivery attendants and postnatal care (PNC) contribute to a high rate of maternal mortality in developing countries. Global health goals still offer a renewed opportunity to see improvements in maternal health [1–3]. It has been argued that attending the specified services on a continuum of care perspective provides a platform for important health care functions, including health promotion, screening and diagnosis, and disease prevention [4–6].

In Ethiopia, one explanation for poor health outcomes among women is the lack of use of modern health care services by a great proportion of women [7]. Even though the overall utilization is low, women are more likely to attend for ANC than to deliver in health facilities [8–11]. This is evidenced by the result of the recently conducted Ethiopian Mini-Demographic and Health survey in 2019; 43% of mothers had four or more ANC visits while less than half of mothers (48%) gave birth in health facilities, and PNC within 2 days of delivery was sought by 34% of mothers [10]. In addition, early entry to ANC would improve the number of consecutive visits that a woman made [12]. However, the analysis of the 2011 Ethiopian Demographic and Health Survey showed that only 26.2% of those attending ANC started their ANC visit during the recommended time (first trimester), with the majority (56.4%) starting during the second trimester and 16.7% starting during the third trimester [2].

In recognition of these problems, the government of Ethiopia identified maternal health services as a key component of the country’s flagship health-extension program [13]. However,, limited intervention studies were conducted on improving maternal health services, and most were m-health based, which require a mother or her relative to own a mobile phone [14]. Some of these studies reported effectiveness in improving maternal health service utilization [15].

A checklist-based box system intervention (CBBSI) was designed with the aim of increasing utilization of maternal health services that could be rolled out both in urban and rural settings. The boxes were designed to fit with the currently implemented focused ANC approach for ANC and the World Health Organization (WHO) recommendation on PNC visits. The basic intention of the trial is to create demand for service utilization and provide dropout tracing through monitoring health service utilization.

## Methods/design

### Design

The study is a double-blind, parallel-group, two-arm cluster randomized controlled trial to assess the effectiveness of CBBSI on improving utilization of maternal health care services in East Gojjam Zone, northwest Ethiopia. The participant flow details are shown in Fig. 1.

**Fig. 1 Fig1:**
[figure not shown]
Participant flow through the trial. CBBSI checklist-based box system intervention

[figure not shown]

**Table 1 Tab1:**
[figure not shown]
Representation of a checklist-based box system intervention using Standard Protocol Items: Recommendations for Interventional Trials (SPIRIT)

*ANC* antenatal care

### Setting

The study will be conducted in East Gojjam zone, one of the administrative zones of the Amhara region in northwestern Ethiopia. According to the 2016 Ethiopian Demographic and Health Survey, the region’s maternal health service utilization for the first and fourth ANC was found to be 67.1% and 31.5%, respectively, health facility delivery was 27.1% and PNC was 18.4% [9]. Debre-markos, the capital city of East Gojjam zone, is located in a northwest direction, 299 km from the national capital Addis Ababa. According to a US Agency for International Development estimate, the population of East Gojjam zone was estimated to be 2,613,835, with a male population of 1,292,042 (49.4%) and a female population of 1,321,788 (50.6%) in 2017 [16].

### The context of the primary health care unit

The Ethiopian health service is structured into a three-tier system, with primary, secondary and tertiary levels of care. The primary level of care includes primary hospitals, health centers and health posts. The primary health care unit is composed of a health center and five satellite health posts. These provide both preventive and curative services to approximately 25,000 people altogether. Health centers serve as a referral center and practical training institution for health extension workers (HEWs). In turn, primary hospitals serve as a referral center for health centers under its catchment areas and a practical training center for nurses and other paramedic health professionals [17].

Ethiopia’s health-extension program is a community-based strategy to deliver health promotion, disease prevention and selected curative health services at the community level. It is a mechanism to provide health services free of charge to all segments of the population in the country by paid HEWs. HEWs are drawn from the community they are going to serve, and are trained for 1 year. Two HEWs per health post are deployed to provide services under the 16 packages by making house-to-house visits. Improving access and utilization of latrines, increasing contraceptive acceptance rates and ANC and PNC, improving health-seeking behavior, expanding vaccination services, improving malaria control and prevention, and reduction of new human immunodeficiency virus infection are some of the major packages that are expected to be delivered by HEWs. HEWs spend 75% of their time on home-to-home visits providing promotional and preventive interventions and 25% of their time at health posts [13, 17]. Even though maternal health services are delivered at different levels of the health system, this trial is focused on improving service delivery in the primary health care units. Using the existing referral linkages between primary health care units, all three contact points (ANC, delivery and PNC) are expected to happen at the health center level (as recommended) where the monitoring box is placed. If the mother made one of the visits, including delivery by her preference, at facilities other than the intervention health center it will be tracked by HEWs and, if it is confirmed, her individual folder will be transferred to the next stage. However, if the mother is permanently moved to another facility/residence, she will be excluded from the study. Since the services are similar for primary hospitals and above, the trial can also be applied to hospitals.

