##### Health center

Once the mothers are linked to a nearby health center, they will be followed for their subsequent attendance of consecutive maternal health care services of ANC (second to fourth visits), skilled birth attendance, and PNC (1–3 visits). This will be checked using a specially designed service utilization monitoring box. This box is a nine-compartment box (Fig. 3); the first compartment is for mothers suspected of being pregnancy using the pregnancy screening checklist from the HEWs. If the mothers arrive and confirm their pregnancy (via HCG test) they will receive the first ANC and their card will be transferred to the next compartment; the same procedure will be followed for the coming consecutive maternal health care service visits. The visits for ANC will follow the four-visit WHO ANC model (i.e., first ANC before 16 weeks of gestation, second ANC at 24–28 weeks, third ANC at 30–32 weeks, fourth ANC at 36–40 weeks); facility delivery is that assisted by skilled health-care providers at the health-center level and above; and visits for PNC are PNC visit 1 at 6 h, PNC visit 2 at 6 days and PNC visit 3 at 6 weeks after delivery. This service utilization monitoring box will help midwives identify mothers who fail to follow the above smooth transition. If a mother is identified as a ‘dropout’, midwives at health centers will communicate to HEWs in the area in which the mother lives. Again, these mothers will be approached for person-centered health education to resume their service within the recommended time interval.

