### Data collection tools and techniques

Data will be collected using a semistructured and pretested questionnaire. The questionnaire used to collect the data was designed by reviewing relevant literature and related national and international standards, and the focus is on educational and ecological assessment, a mother’s experience related to pregnancy, delivery and PNC, social and epidemiological assessment, behavioral and environmental assessment, general social support and social capital and health service quality components. This will be translated to an Amharic version (the local language of the study area).

The translated version was uploaded to KoBo toolbox, and an open data kit (ODK) will be used to collect data. The study will use face-to-face interviews and the data will be collected using mobile devices in front of each selected mother’s home. Completed questionnaires will be saved in the mobile devices and will be sent to the central server immediately after completing the interview. In cases where the data collectors cannot complete the questionnaires and when an internet connection cannot be accessed the completed questionnaires will be forwarded when there is an internet connection available. The data collection will be managed directly from the Jimma University server. Each data collector and supervisor has a code to make data management easy. If a study participant in either arm moves from the study area before the study is completed, they will be registered as dropouts and lost to follow-up. This trial will have two phases of data collection: baseline study (before the intervention is introduced) and end-line study (after the intervention is introduced).

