### Analysis plan

Data from the trial will be analyzed by an intention-to-treat analysis at both cluster and participant levels. Participants will be assigned to the cluster they were resident in at the time the trial began. The primary data analysis will take place at the cluster level. Risk ratios will be computed at the cluster level, and the results of this cluster summary will be compared using *t* tests. Primary and secondary outcomes will be compared between intervention and control groups with random effects logistic regression models, taking account of clustering/correlation. All estimates will be presented with 95% confidence intervals. STATA version 13.0 will be used to run the analysis.

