### Outcome measures

Primary outcomes are the continued utilization of maternal health care service (ANC to PNC), mothers attending the fourth ANC visit, mothers delivering at health facilities assisted by skilled care providers, and mothers attending the third PNC visit at 6 weeks after delivery.

Secondary outcome measures will assess whether the trial has an effect on early initiation of ANC (initiation of ANC before 16 weeks of gestation), and utilization of the first ANC (first ANC visit attendance, regardless of the time of initiation).

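### Excluding enrolled women who permanently change facility or residence contradicts the stated intention-to-treat analysis, most clearly for a woman who transfers her care but stays in the area

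*Protocol article*

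**What the plan says.** Four parts of the protocol article bear on a woman who moves after enrolment.

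- **The context of the primary health care unit.** A single visit or delivery at a facility other than the intervention health center is credited: "it will be tracked by HEWs and, if it is confirmed, her individual folder will be transferred to the next stage". The next sentence sets a different rule for a lasting change: "if the mother is permanently moved to another facility/residence, she will be excluded from the study".
- **Data collection tools and techniques.** If a participant in either arm "moves from the study area before the study is completed, they will be registered as dropouts and lost to follow-up". Data come from face-to-face interviews at the mother's home, at baseline and end-line.
- **Analysis plan.** "Data from the trial will be analyzed by an intention-to-treat analysis at both cluster and participant levels", and "Participants will be assigned to the cluster they were resident in at the time the trial began".
- **Outcomes.** Under Outcome measures, "Primary outcomes are the continued utilization of maternal health care service (ANC to PNC), mothers attending the fourth ANC visit", together with skilled facility delivery and the third postnatal visit. Under Health center, "facility delivery is that assisted by skilled health-care providers at the health-center level and above", so delivery is not limited to the linked health center.

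**The concern.** Intention-to-treat keeps the randomised groups together whatever happens afterwards. Clusters were allocated, staff trained and boxes distributed before women were enrolled, so any removal after enrolment is also after randomisation. The exclusion is triggered in part by where a woman obtains care, and the primary outcomes are themselves measures of care use. If the women removed differ in service use from those kept, and are removed in different proportions or are of different kinds in the two arms, the comparison is no longer between the randomised groups. A larger sample would not cure that.

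There is also a practical problem. Excluded, lost to follow-up, and retained in the original cluster imply different denominators, and an analyst cannot apply all three to the same woman.

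**Working it through.** **1. The rules side by side.**

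| Event after enrolment | Primary health care unit section | Data collection section | Analysis plan |
|---|---|---|---|
| One confirmed visit or delivery elsewhere | Credited | Not addressed | Retained |
| Permanent change of facility, same area | Excluded | Not addressed | Retained |
| Change of residence, leaves the study area | Excluded | Dropout, lost to follow-up | Retained in original cluster |
| Change of residence within the study area | Excluded | Not addressed | Retained in original cluster |

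The second row is the sharpest conflict. The dropout rule does not reach this woman. Delivery at any health center or above counts for her, and she still lives where the interviewer will call. Her data are obtainable, but the exclusion discards them.

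**2. Is removal related to the outcome?** For a change of facility, yes: it is a care-seeking event in a trial of care use. For a change of residence, a link is plausible but the document does not state one.

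**3. Could detection differ by arm?** The rule is framed around the intervention health center and its folders, and the Control section says that controls have no monitoring box. Unequal detection of facility changes is therefore possible. It is an inference; no passage says that changes in the control arm go unrecorded.

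**4. Illustrative size.** The plan gives no figure for movers, so there is none to reproduce. Let p be the true outcome rate in all enrolled women, identical in both arms (no effect), m the proportion excluded, and r the outcome rate among those excluded. The rate among those kept is (p − m·r)/(1 − m). All m and r below are assumptions.

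- Fourth antenatal visit, p = 31.5% (regional figure, Setting), r = 10%. m = 5%: (0.315 − 0.005)/0.95 = 32.6%. m = 10%: 0.305/0.90 = 33.9%. m = 20%: 0.295/0.80 = 36.9%. With 5% excluded in one arm and 10% to 20% in the other, the spurious difference is 1.3 to 4.2 points, and the arm that loses more looks better.
- Facility delivery, r = 70%, with 5% v 15% excluded. At p = 48% (national figure, Background): 0.445/0.95 = 46.8% v 0.375/0.85 = 44.1%, or 2.7 points. At p = 27.1% (regional figure, Setting): 0.236/0.95 = 24.8% v 0.166/0.85 = 19.5%, or 5.3 points. Here the arm that loses more looks worse.
- Third postnatal visit, p = 16% (sample size section), r = 0, with 15% v 5% excluded: 0.16/0.85 = 18.8% v 0.16/0.95 = 16.8%, a risk ratio of 1.12, or 0.89 with the arms reversed.
- Zero bias: if r = p, then (p − m·p)/(1 − m) = p for any m. If m and r are the same in both arms, the difference is also zero.

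**5. Power is not the issue.** With 15 clusters of 40 per arm and the stated intracluster correlation of 0.04849, the design effect is 1 + 39 × 0.04849 = 2.891 and the effective size is 600/2.891 = 207.5 per arm. For 16% v 28% (reading the 12% increase as percentage points) at two-sided 5%, power is 84.2%. Losing 10%, 20% or 30% of women leaves 82.9%, 81.2% or 79.1%.

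**The case against.** The best defence is context. The sentence is not in the Analysis plan; it closes a description of how folders pass through the monitoring box. Excluded may mean only that box follow-up stops, with the dropout rule giving the woman's status and the Analysis plan governing the denominator. The slash between facility and residence might also have been meant for women who change both. Either reading is possible, but the text says excluded from the study, and the dropout rule does not cover a woman who changes facility and stays. If a milder meaning was intended, the wording still has to change.

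Several limits do stand:

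- A reader might infer that any woman who delivers in a hospital is dropped. The preceding sentence credits such a delivery once confirmed; only a permanent transfer triggers the exclusion, and nothing shows how common that is.
- A reader might infer that exclusions will be found mainly in the intervention arm. The dropout rule applies to both arms, the interviews are described without any difference by arm, and a woman who has left the area is equally absent in either.
- The illustrative differences depend on the rates chosen, including their sign, and equally admissible rates give zero.
- Handling of missing outcomes is commonly left to a statistical analysis plan, so its absence here is not a fault. It enters only as part of the repair.

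**Conclusion.** The point holds as a contradiction. Read as written, the exclusion cannot stand with intention-to-treat by original cluster, and the data collection section does not settle the matter. It is plainest for a woman who permanently transfers her care but remains in the area, because she can attain the primary outcomes and be measured, and is removed for her care-seeking.

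The document supports no stronger conclusion. It does not show that the trial will be biased, in which direction, or by how much. The differences of 1.3 to 5.3 points above are arithmetic on assumed rates; they show that the bias could be a material fraction of the 12-point target, and it could also be nil. Unequal detection by arm is a reasonable suspicion and not a stated fact. The link to the outcome is direct only for a change of facility.

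**What to change.** - In the primary health care unit section, delete the exclusion, or state that it ends only follow-up through the monitoring box.
- Reconcile that section, the data collection section and the Analysis plan so that every enrolled woman stays in the analysis, in the cluster where she lived at enrolment. Fixing membership at enrolment also removes a small ambiguity about when the trial began, since recruitment runs from 22 November 2018 to about October 2019.
- Count care at any qualifying facility by the same rule in both arms.
- Treat women who cannot be reached at end-line as having missing outcomes, not as excluded, with one sensitivity analysis counting them as non-attenders.

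The cost is wording in three sections, slightly more missing data to handle, and one extra analysis. No tracing outside the study area is required, and the home interviews needed for women who change facility but stay are already planned.

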### Participant eligibility criteria

The participants for this trial will be pregnant mothers residing in three of the selected districts of East Gojjam zone (Debre-Markos, Gozamin and Machakel districts). Recruitment will pass a two-stage screening process. Using a preset criterion, the initial screening will be done at the community level using the pregnancy screening checklist from Stanback et al [18]. (last menstrual period for gestational age dating), and mothers having a suspected pregnancy will have a laboratory confirmation at the health center. Those having a gestational age of 16 weeks will be recruited for the study. Mothers who fulfill the above criteria but who have severe psychological illness which could interfere with consent and study participation, those who have severe clinical complications that need hospitalization and mothers who need a special type of ANC follow-up, other than the recommended focused ANC, will be excluded from the study.

### Sample size determination

The sample size was calculated based on the recommendations of sample size calculations for cluster randomized controlled trials with fixed number of clusters [19] by using the following assumptions: utilization of the third PNC in the control group is 16% based on a previous study [20], the number of clusters available is 30 (15 clusters per arm), with 95% confidence interval and 80% power, and an intracluster correlation coefficient of 0.04849 [21]. The sample size was calculated to determine the number of observations required per cluster for a two-sample comparison of proportions (using normal approximation) using STATA software. Assuming individual randomization, the sample size per arm is 194; allowing for cluster randomization, the average cluster size required is 40. A total of 1200 pregnant mothers (600 in the intervention and 600 in the control groups) will be recruited to detect a 12% increase in the utilization of ANC visit four, skilled birth attendance and PNC. The outcome is treated as a binary measure.

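### The cluster size of 40 does not follow from 194 per arm, 15 clusters per arm and the stated ICC, which give 33; the named normal approximation does not give 194 either

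*Protocol article*

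**What the plan says.** Everything at issue is in the protocol article, section Sample size determination. It assumes that "utilization of the third PNC in the control group is 16% based on a previous study", 30 available clusters (15 per arm), "an intracluster correlation coefficient of 0.04849", and a calculation "with 95% confidence interval and 80% power". The method is given as a "two-sample comparison of proportions (using normal approximation) using STATA software", following published recommendations for trials with a fixed number of clusters.

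Two results follow: "Assuming individual randomization, the sample size per arm is 194; allowing for cluster randomization, the average cluster size required is 40". The recruitment target is then 30 × 40 = 1200 women, split equally between the arms. The stated purpose of that number is "to detect a 12% increase in the utilization of ANC visit four, skilled birth attendance and PNC".

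The section does not print the intervention-arm proportion, does not say whether 12% is absolute or relative, and mentions no adjustment for losses, unequal cluster sizes or a small number of clusters. The Analysis plan section places the primary analysis at the cluster level, with t tests on cluster summaries.

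**The concern.** The article prints the inputs, names the method and prints the results, so a reader can check one against the other. They do not agree at either step. The second step matters more: it uses only figures in the text (194, 15 clusters per arm, the ICC) and does not depend on how the effect size is read.

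The cluster size of 40 fixes the 1200 women to be recruited. Because the route to it is not given, nobody can tell whether the surplus over 33 is a margin for women who move away, an allowance for unequal clusters, a correction for the cluster-level t test, or a slip. The article expects some loss: women who move permanently are excluded (The context of the primary health care unit) or counted as lost to follow-up (Data collection tools and techniques). How much loss the design can absorb depends on which explanation is right.

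**Working it through.** **Inputs from the document.** Control proportion 16%; increase 12%; 95% confidence; 80% power; ICC 0.04849; 15 clusters per arm; 194 per arm; 40 per cluster.

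**Assumptions.** Two-sided 5% test; 12% read as percentage points, so 16% v 28%; equal cluster sizes unless stated. A relative 12% (16% to 17.92%) would need 5997 per arm, so the printed 194 rules it out.

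**Step 1: the individually randomized size.** The variance sum is 0.16 × 0.84 + 0.28 × 0.72 = 0.336 and the difference is 0.12.

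- Unpooled normal: (1.960 + 0.842)² × 0.336 / 0.12² = 183.1.
- Pooled normal (mean proportion 0.22): 185.9, so 186.
- Pooled with continuity correction: 202.2, so 203.
- Unpooled, with a t quantile in place of 1.960: 194.9 on 28 degrees of freedom (t = 2.048), 194.1 on 30 (t = 2.042).

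The plan's 194 is reproduced only by the t-based variant, which is not the normal approximation that the text names.

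**Step 2: from 194 to the cluster size.** With k clusters per arm, setting k × m = n × [1 + (m − 1) × ICC] and solving for m gives

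m = n(1 − ICC) / (k − n × ICC).

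For n = 194 and k = 15: 194 × 0.95151 = 184.59; 15 − 194 × 0.04849 = 5.593; m = 184.59 / 5.593 = 33.0.

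Other starting sizes with k = 15:

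| n per arm | m |
|---|---|
| 186 (pooled normal) | 29.6 |
| 194 (as printed) | 33.0 |
| 194.9 (t, 28 df) | 33.4 |
| 202.2 (continuity-corrected) | 37.0 |

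None reaches 40. Routes from 194 that do come close each need something the text does not contain:

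- 14 clusters per arm: 184.59 / 4.593 = 40.2.
- Coefficient of variation of cluster size about 0.32 (replace n × ICC by n × ICC × (1 + CV²)): 39.9.
- A 20% add-on: 33.0 × 1.2 = 39.6.

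**Step 3: size of the gap.** 30 × 33 = 990 against 30 × 40 = 1200: 210 women, or 21% more than the printed inputs require.

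**Step 4: power for the third PNC visit, 16% v 28%.** At 40 per cluster the design effect is 1 + 39 × 0.04849 = 2.891 and the effective size is 600 / 2.891 = 207.5 per arm. The standard error is √(0.336 / 207.5) = 0.0402, and 0.12 / 0.0402 = 2.98. Normal power is 84.7% (84.2% with the pooled variance under the null). The noncentral t on 28 degrees of freedom gives 82.1%.

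| Women per cluster | Power by t, 28 df |
|---|---|
| 33 | 79.5% |
| 34 | 79.9% |
| 35 | 80.3% |
| 40 | 82.1% |

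By the t test the requirement is therefore about 35 per cluster, which leaves room to lose 5 of 40 women (12.5%) before power drops below 80%.

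**The case against.** The strongest reply is that nothing is harmed. The printed design exceeds its own target, recruitment began in November 2018, and no enrolment figure would change. This stands, and it limits the point to a correction of the text.

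A second reply is that 194 need not be wrong. A t quantile on about 28 degrees of freedom suits the planned cluster-level t test and gives 194.9. Rounded inputs could also produce it: a pooled normal calculation gives 194.6 for 16% with an 11.7-point rise and 194.2 for 16.4% with 11.8 points. This stands too. A reader might infer that 194 is an arithmetic error; the document does not establish that. What remains is that the named method, with the inputs as printed, does not give the printed number.

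A third reply is that the step from 33 to 40 may be an ordinary allowance for loss that a condensed article leaves to the full protocol. That may be so, but the article presents 40 as the size needed once clustering is allowed for, and gives 15 clusters per arm. Any of the three routes above has to be supplied by the reader, and they have different consequences. If the surplus covers unequal clusters, it is not also available for loss.

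**Conclusion.** The point holds as a minor discrepancy in a figure on which recruitment rests. From the printed 194, ICC and 15 clusters per arm, the formula requires 33 per cluster, not 40. The normal approximation gives 183 to 186 per arm, not 194.

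A reader might go further and conclude that the 80% power is not delivered. The document does not support that for the third PNC visit: 40 per cluster gives about 85% (normal) or 82% (t, 28 df), so the error is on the safe side. The margin under the planned t test is thin, at about 2 percentage points before any loss.

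These figures assume an absolute 12-point increase, a two-sided 5% test, equal cluster sizes and the stated ICC. They concern only the third PNC visit, the one outcome for which the section gives a control proportion.

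**What to change.** Restate the sample size section, with no change to enrolment:

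- Give the comparison as 16% v 28%, an absolute increase of 12 percentage points.
- Name the formula that produces 194, including any t quantile and its degrees of freedom, or replace 194 with 186 (pooled normal approximation).
- State the correction that leads to 40 if one was used. If none was, say that the formula requires 33 per cluster from 194 by normal approximation (30 if 186 is adopted) and about 35 by the cluster-level t test. Add that the 40 recruited gives about 85% power (normal) or 82% (t, 28 df) for the third PNC visit before loss to follow-up.

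The figure of 33 should not stand alone as the requirement, because under the planned t test it gives 79.5%. The cost is a few sentences. The small downside is that published figures change and the limited margin for loss becomes visible.

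### The 80% power for a 12-point increase was derived for third PNC only; for ANC visit four and skilled delivery the same design gives about 69–75% at the regional rates and 66–70% at the national rates

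*Protocol article*

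**What the plan says.** The Sample size determination section of the protocol article takes as its control rate that "utilization of the third PNC in the control group is 16% based on a previous study". It adds 30 available clusters (15 per arm), "with 95% confidence interval and 80% power", and "an intracluster correlation coefficient of 0.04849". From these it reports 194 per arm under individual randomization, an average cluster size of 40, and 1200 mothers in all, "recruited to detect a 12% increase in the utilization of ANC visit four, skilled birth attendance and PNC". No control rate for ANC visit four or for delivery enters the calculation.

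Both are primary outcomes under Outcome measures and in the abstract ("Achieving four antenatal care visits, health facility delivery, and postnatal care visits at 6 weeks after delivery were treated as primary outcomes"). The document gives rates for them elsewhere. Setting reports for the region: "first and fourth ANC was found to be 67.1% and 31.5%, respectively, health facility delivery was 27.1% and PNC was 18.4" percent. Background reports nationally for 2019: "43% of mothers had four or more ANC visits while less than half of mothers (48%) gave birth in health facilities".

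**The concern.** For a fixed absolute difference, the variance of a comparison of two proportions grows as the rates approach 50%. The 16% used for sizing is lower than every rate the document quotes for ANC visit four or facility delivery, so a sample just large enough for third PNC is too small for the same 12 points on the other two. The protocol nevertheless gives all three the same detectable increase.

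The stake is how a null result is read. A non-significant finding on ANC visit four or delivery would be taken as coming from a trial with 80% power for 12 points, when the chance of missing a true 12-point gain is roughly one in four to one in three.

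**Working it through.** **Inputs.** Sample size determination gives 15 clusters per arm, 40 women per cluster, ICC 0.04849, 80% power and a 95% confidence level (taken as two-sided 5%). Control rates are 16% for third PNC (same section), 27.1% for delivery and 31.5% for ANC visit four (Setting), and 48% and 43% for the same two (Background). The 12% is read as percentage points: a relative 12% (16% to 17.92%) would need 5997 per arm, which cannot be squared with 194.

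**The plan's own figure.** For 16% against 28%, the individually randomized size per arm is 186 (pooled normal), 184 (unpooled), 203 (continuity-corrected), or 194.9 (unpooled with a t critical value on 28 df). The stated 194 is close to the last. With n = 194, the fixed-cluster formula m = n(1 − ICC)/(k − n × ICC) gives 33.0 at k = 15 and 40.2 at k = 14. The exact route to 194 and 40 is therefore not visible, but the plan's 600 per arm is enough for third PNC, as the first row of the table shows.

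**Effective size.** Design effect = 1 + 39 × 0.04849 = 2.891. Effective n per arm = 600/2.891 = 207.5.

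**Power for +12 points.** Standard error = √[(p1(1 − p1) + p2(1 − p2))/207.5]. The ratio 0.12/SE is referred to the normal distribution, or to a noncentral t with 28 df. The t version is shown because the Analysis plan makes a cluster-level t test the primary analysis; the normal version is shown because the sample size section says it used a normal approximation.

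| Outcome and control rate | 0.12/SE | t, 28 df | Normal, pooled | Normal, unpooled |
|---|---|---|---|---|
| Third PNC, 16% | 2.98 | 82.1% | 84.2% | 84.7% |
| Delivery, 27.1% (regional) | 2.62 | 71.5% | 74.0% | 74.5% |
| ANC visit four, 31.5% (regional) | 2.54 | 69.0% | 71.5% | 72.1% |
| ANC visit four, 43% (national) | 2.46 | 66.2% | 68.8% | 69.3% |
| Delivery, 48% (national) | 2.47 | 66.5% | 69.0% | 69.5% |

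**Difference detectable at 80% power**, over the four ANC and delivery rates: about 12.9–13.7 points by the normal approximation, and 13.3–14.1 points by the t test.

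**Sensitivity to the ICC.** Holding 15 clusters of 40 and 12 points, 80% is reached for these two outcomes at an ICC of about 0.031–0.039 (normal) or 0.028–0.035 (t), against the stated 0.04849.

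**The case against.** The case on the other side is that this is one imprecise sentence in a design that otherwise stands. On the protocol's own normal approximation and the rates for its own region, power is about 72–75% and the detectable difference about 13 points against 12. The 66% figures need both the t test and national rates, and the protocol cites those rates as background, not as planning values for these districts. The ICC comes from a cited source and is not tied to an outcome, so the values for ANC visit four and delivery may be lower.

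Much of this stands. The regional figures are the fairer lead, the national ones mark the lower end of the range, and the common ICC is an assumption. None of it rescues the sentence: power is below 80% for both outcomes at every rate the document quotes and by each method above, and no separate calculation is given for them.

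Stronger readings are tempting, but the document does not support them:

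- A reader might infer that every enrolled woman has already made a first ANC visit, since Screening and enrollment gives that visit on the day of recruitment, and so raise the control rates further. But Outcome measures makes first ANC attendance a secondary outcome, which would mean little if all had attended. Rates conditional on a first visit are speculative.
- A reader might infer that several primary outcomes mean any one significant test would be claimed as success. Outcome measures does list one that the abstract does not ("Primary outcomes are the continued utilization of maternal health care service (ANC to PNC), mothers attending the fourth ANC visit" and so on), but that mismatch is a separate matter. The protocol states no such success rule, and error control across outcomes is commonly left to an analysis plan, which is not shown.
- A reader might conclude that the trial is too small and must be enlarged. The third-PNC calculation holds, and the shortfall elsewhere is moderate.

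**Conclusion.** The point holds as a power statement that is wrong for two of the three outcomes it names. For third PNC the 80% is met (82–85%). For a 12-point increase at the regional rates, power is about 72–75% for facility delivery and 69–72% for ANC visit four; at the national rates it is about 66–70% for both.

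This rests on three assumptions: 12% means percentage points, the single ICC of 0.04849 applies to all outcomes, and control rates lie within the range the document quotes (27.1–48%), since rates for the three districts are not given. No loss to follow-up is deducted.

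**What to change.** Reword the Sample size determination section in three respects:

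1. State that 80% power for a 12-percentage-point absolute increase applies to third PNC at a 16% control rate.
2. For ANC visit four and skilled delivery, give power of about 69–75% at the regional rates (66–70% at the national rates), or a detectable difference of about 13–14 points at 80% power.
3. State that one ICC, 0.04849, is assumed for all outcomes.

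This is a change of wording only. It needs no extra women or clusters and leaves the list and standing of the primary outcomes as they are. The cost is a less favourable stated power for two primary outcomes.
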